#### Objective 2: additional prognostic factors

A new risk prediction model for rupture will be developed using the total data set, including the additional possible risk factors. The Cox regression model will be used for risk of rupture. The absolute risks can be estimated at relevant time intervals, 2, 5 and 10 years. Numbers of missing values will be summarised for each factor. Multiple imputation will be used to replace missing values. Discrimination of the final model will be assessed with Harrell’s C-statistic. Internal validity will be assessed by bootstrap resampling.

#### Objective 3: long-term rupture rates

All patients, including those who underwent aneurysm occlusion, will be included in time-to-event analysis which will cover the whole duration of available follow-up. This will include Kaplan-Meier and proportional hazards models for univariate and multivariate survival curve fitting. A cumulative hazard plot will be used to assess if rupture risk is constant or varies with time from diagnosis.

Once the cohort is established, funding will be sought for repeated searches at regular intervals (5 yearly) to update models and provide progressively long-term rupture rates.

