Patient identifiable details (name, date of birth, post code, NHS/CHI number) will be securely sent by each neurosurgery unit to the coordinating centre for consolidation and linkage to the national databases for hospital admissions. These databases are: Hospital Episode Statistics (HES), Patient Episode Database for Wales (PEDW) and Scottish Morbidity Database (SMD). These databases also link to the Civil Registrations—Death and National Registry Scotland for death records. Patients will be linked to hospital admissions based on International Classification of Diseases 10th Revision (ICD-10) diagnosis codes for intracranial haemorrhages and OPCS4 codes for aneurysm occlusion treatments. These databases record every hospital admission in their respective country and thus using this as the outcome source, combined with death records, will allow identification of every aneurysmal subarachnoid haemorrhage (aSAH) regardless of whether they were managed in a neurosurgery unit, a district general hospital, migrated out of the region in which their UIA was diagnosed, or died in the community. The number of patients with aSAH who are not captured by this method, either because they do not present to hospital or emigrate out of the UK, is expected to be very small. Rupture rates can be adjusted based on national emigration rates.

Patients will be censored if there is any occlusive treatment of the UIA or patient death. Occlusive treatment includes either microsurgical or endovascular techniques either partial or complete. If none of these censoring events are observed, then they will be censored on the day the cohort is submitted to the HES/PEDW/SMD databases.

The ICD-10 codes to be searched for rupture events have been selected in accordance with the UK Biobank stroke research and include: aSAH (I60.1-9), intracerebral haemorrhage (I61.0-9), traumatic subarachnoid haemorrhage (S06.6) and spontaneous subdural haemorrhage (I62.00-I62.02).^16^ The use of codes beyond those for aSAH will capture any hospital admissions for aneurysm rupture which have resulted in other forms of intracranial bleed or have been miscoded.

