### Outcomes

#### Primary end points

The primary end point is rupture of an untreated UIA at a timepoint at least 1 day following diagnosis. A rupture event is defined as either radiological evidence of aSAH in a distribution consistent with the aneurysm location, CSF spectrophotometry positive for xanthochromia per the local unit’s reference range or death certificate stating subarachnoid haemorrhage in causes of death 1a-c.

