### Statistical analysis

#### Objective 1: PHASES validation

The PHASES study provides the coefficients from their Cox regression model and baseline survival at 5 years which allows the absolute 5-year risk of rupture to be calculated for all patients who are not censored before 5 years. Time to censoring will be calculated (whichever is soonest of the date of treatment, date of death or the HES/PEDW/SMD search date) to ensure 5 years of follow-up if rupture has not occurred. Discrimination will be assessed using Harrell’s C-index of concordance and Royston and Sauerbrei’s D statistic. Calibration will be assessed at the 5-year time point using the method by Royston.^19^ These will be used to calculate the number of SAH events per 5 years for each PHASES score (≤2 to 12+) and expressed as a percentage with 95% CI to compare with the PHASES estimates.

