## Discussion

Although the natural history of UIA has been previously investigated with multiple prospective cohort studies, the rupture rate has varied significantly between these. The design of the ROAR study addresses many of the criticisms of these previous natural history studies. ISUIA^7^ is the first natural history study and is drawn from a population that is genetically closest to that of the UK. However, its results are subject to selection bias with 71% of their UIA being treated either before inclusion or during follow-up. It is not known if that selection was random or based on a feature associated with risk such as aneurysm irregularity. It is therefore not known how the rupture rates in the remaining potentially lower-risk patients translate to the general population. The UK has a much lower treatment rate of UIA (approximately 20%). This is one of the lowest rates in a high-income country making it the ideal setting for a natural history study. It remains however that there will be some treatments performed during the study which inevitably will produce some selection bias that cannot be eliminated. Other countries with lower treatment rates are likely to also have low availability of imaging and hence much lower case identification limiting the cohort size and introducing different biases.

There is also a risk of selection bias in ROAR arising from the methods employed for patient identification. Patients in whom no MDT, clinic notes or radiology report was created would be effectively excluded. These are also the patients more likely to not undergo treatment. However, our survey of UK neurovascular surgeons suggest it is only a very small minority that are not discussed at MDT or seen in a neurosciences clinic. This was also borne out in pilot studies in the development of the protocol. The timeframe for searching patients within a unit’s available records creates the potential for introducing prevalence-incidence selection bias. The ROAR study will mitigate this by identifying patients as *new* or *follow-up* based on whether or not the UIA was diagnosed during that unit’s search window and use the identifying document dates accordingly.

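### Objective 3 does not say whether treated patients are censored at occlusion; read literally, it conflicts with the study's censoring rule and its untreated-aneurysm end point

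*Protocol article*

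**What the plan says.** Four places in the protocol article bear on this.

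- **Study design** gives a rule tied to no single objective: "Patients will be censored if there is any occlusive treatment of the UIA or patient death". Treatment is defined broadly: "Occlusive treatment includes either microsurgical or endovascular techniques either partial or complete". The database date is only a fallback: "If none of these censoring events are observed, then they will be censored on the day the cohort is submitted".
- **Primary end points**: "The primary end point is rupture of an untreated UIA at a timepoint at least 1 day following diagnosis".
- **Objective 1** repeats treatment as a censoring date ("whichever is soonest of the date of treatment, date of death or the HES/PEDW/SMD search date") and restricts its analysis set: the published PHASES model "allows the absolute 5-year risk of rupture to be calculated for all patients who are not censored before 5 years".
- **Objective 3**: "All patients, including those who underwent aneurysm occlusion, will be included in time-to-event analysis which will cover the whole duration of available follow-up". The methods listed are Kaplan-Meier and proportional hazards models, with a cumulative hazard plot to judge whether risk changes with time since diagnosis.

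The Objective 3 text neither restates nor lifts the censoring rule, and it does not say that time after treatment counts. The Discussion puts the UK treatment rate at approximately 20% and says that treatments during the study "inevitably will produce some selection bias that cannot be eliminated".

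**The concern.** Objective 3 singles out patients who had an occlusion, includes them, and extends the analysis over all available follow-up. Outcomes come from national admission and death records, which continue after an occlusion, so available follow-up can naturally be taken to run past treatment.

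An analyst who took it that way would keep treated patients in the risk set while a rupture of the treated aneurysm could no longer count towards the end point. Event-free time would be added to the denominator and the long-term curve would be too low. The hazard would also appear to fall as treated patients built up in the risk set, which is the feature the cumulative hazard plot is meant to examine. Another analyst, applying the Study design rule, would draw a different curve from the same data. Long-term risk is one of the study's three objectives, so the text should allow only one of these.

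**Working it through.** The protocol gives no figure for Objective 3 to reproduce. The check sets out the two readings and then sizes the difference.

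**Two readings**

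- *A, censor at treatment.* Treated patients enter and leave the risk set at occlusion. This agrees with Study design, the end point and Objective 1.
- *B, keep at risk.* Treated patients stay in until death or the database date. This conflicts with Study design and adds time outside the untreated-aneurysm end point.

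**Inputs from the protocol**

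- Proportion treated: 0.20 (Discussion).
- Maximum follow-up: T = 15 years (Discussion).
- Annual rupture rate λ, three values: 51/(1692 × 4.1) = 0.735% (ISUIA, Sample size); 1.4% (Introduction); 60/4010 = 1.50% (feasibility work, Sample size).

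**Assumed, not in the protocol**

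- Delay from diagnosis to treatment: d = 0 to 2 years.
- Rupture rate after treatment relative to untreated: q = 0 to 0.25. A strict reading of the end point corresponds to q = 0 for the treated aneurysm.
- Constant hazard, and treatment unrelated to rupture risk.

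**Cumulative risk at 15 years**

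Reading A: F = 1 − exp(−λT).

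Reading B: 0.8 × F + 0.2 × [1 − exp(−λd − qλ(T − d))].

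Worked case, λ = 1.4%, d = 0, q = 0: F = 1 − exp(−0.21) = 18.94%. Reading B is 0.8 × 18.94% + 0 = 15.15%, which is 20% lower.

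Other extreme, λ = 1.4%, d = 2, q = 0.25: the exponent is 0.028 + 0.25 × 0.014 × 13 = 0.0735, so the treated fifth has risk 7.09%. Reading B is 0.8 × 18.94% + 0.2 × 7.09% = 16.57%, which is 12.5% lower.

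| λ per year | A | B (d = 0, q = 0) | B (d = 2, q = 0) | B (d = 2, q = 0.25) |
|---|---|---|---|---|
| 0.735% | 10.44% | 8.35% (−20.0%) | 8.64% (−17.2%) | 9.11% (−12.7%) |
| 1.4% | 18.94% | 15.15% (−20.0%) | 15.71% (−17.1%) | 16.57% (−12.5%) |
| 1.50% | 20.10% | 16.08% (−20.0%) | 16.67% (−17.1%) | 17.59% (−12.5%) |

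**Cross-check on the crude rate**

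With no countable event after treatment, both readings have the same events, so the rate ratio B/A is the ratio of person-time: [(1 − p)T + pd]/T. For p = 0.2 and an assumed d of 0.5 years this is (4 + 0.1)/5 = 0.82 at 5 years and (8 + 0.1)/10 = 0.81 at 10 years, an understatement of 18 to 19%. For p = 0.1 it is 0.91 and 0.905; for p = 0.3 it is 0.73 and 0.715.

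**Shape of the hazard**

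A simulation with a true constant rate of 1.40% per year, 20% assigned to treatment at a uniform time in years 0 to 2, and q = 0 gave:

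- Reading A: 1.40% per year overall and 1.40% in years 10 to 15.
- Reading B: 1.12% per year overall and 1.08% in years 10 to 15.

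The timing follows by arithmetic. Under B the apparent hazard after year 2 is λ times the untreated share of those at risk. The treated group at risk stays at 0.2 × (1 − exp(−0.028))/0.028 = 0.197. The untreated group is 0.8 × exp(−0.014t): 0.778 at year 2 and 0.648 at year 15. The apparent hazard is therefore 1.4% × 0.778/0.975 = 1.12% at year 2 and 1.4% × 0.648/0.846 = 1.07% at year 15. Most of the false fall happens while treatments are being given, followed by a slow drift.

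**The case against.** The strongest reply is that the sentence only says who enters the analysis. Study design sets a general rule, and Objective 3 does not withdraw it. Objective 1 calculates absolute risk only for patients not censored before 5 years, so those treated early drop out; Objective 3 brings them back because survival methods can use partial follow-up. On that view, available follow-up ends at the censoring event and the sections agree. This stands. A reader might infer that the protocol definitely counts post-treatment time and will dilute its rates; the text does not establish that, and the simulation shows that including treated patients while censoring them at treatment causes no dilution.

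Other limits also stand:

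- The 20% is a national rate, not a cohort figure, and the protocol gives no time to treatment.
- A reader might infer that the gap between A and B widens if riskier aneurysms are treated. On the crude rate with no countable events after treatment it does not, because the events are the same under both. Selective treatment matters against another target, the untreated risk of the whole cohort, which censoring at treatment does not recover either.
- It is too strong to say that no end point can occur after a patient's occlusion. Records carry an aneurysm-level number (Data transmission and editing), and a patient may have a second, untreated aneurysm.
- A reader might infer that the Discussion wrongly calls treatment selection irreducible. It says the bias cannot be eliminated, which is true and compatible with reducing it.

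What the reply does not remove is that Objective 3 names treated patients and all available follow-up without referring back to the censoring rule, whereas Objective 1 restates it.

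**Conclusion.** The point holds as an ambiguity to be resolved, not as a proven contradiction. On its literal wording Objective 3 conflicts with the Study design rule and the untreated-aneurysm end point; on a reasonable alternative reading it does not.

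If post-occlusion time were counted, 15-year rupture risk would be understated by about 12 to 20% in relative terms (17 to 20% if no post-treatment rupture counts). A constant hazard of 1.40% per year would appear to fall to about 1.1%. These sizes rest on 20% treated, the assumed ranges for delay and post-treatment rate, a constant hazard, and treatment unrelated to risk. The shortfall is large enough to affect a long-term risk estimate intended for counselling patients.

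**What to change.** Reconcile Study design, Primary end points and Objective 3 by rewording Objective 3. For example: all patients, including those later treated, contribute time from entry until the earliest of rupture, first occlusive treatment, death or end of observation; no later time is counted. If an analysis that includes post-treatment time is also wanted, report it separately and label it rupture under current management, because it answers a different question.

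Optionally, because treatment is selective, add a sensitivity analysis with inverse-probability-of-censoring weights built from the collected predictors. It may reduce, but will not remove, the bias that the Discussion acknowledges; that statement can stay as written.

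The required change costs one sentence and no new data. The optional analysis costs one weighted model on data already collected.

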## Methods and analysis

### Objectives

This study has three objectives:

To measure the accuracy of the PHASES score at predicting UIA rupture rates in the UK population.To develop a new, more personalised, predictive model for aneurysm rupture incorporating additional covariates thought to influence risk.To measure aneurysm rupture risk over time periods >5 years.

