The largest UIA studies are based on Japanese populations and the study with the least bias on a Finnish population. Both observed higher rates of aneurysm rupture than ISUIA. Although it has been assumed ethnicity is a risk factor for rupture and therefore included in the PHASES score, it is not known if the different rupture rates in these studies were due to differences in genetics, environment or study design (and consequently biases). The ROAR study will observe rupture rates in a UK population which removes any concerns over the influence of ethnicity in the results and makes it generalisable for UIA decision making in patients in the UK. Given the use of national-level databases, ROAR is designed as a single country study and as a result there are limitations to its generalisability outside the UK. However, the UK’s population probably more closely resembles most European and North American countries than Japan or Finland.

With the exception of the study by Juvela *et al*,^9^ the follow-up lengths of previous UIA natural history studies are <5 years. Patients are generally not interested in such short-term risks and want to know their lifetime risk. Unfortunately, it is not known if risk is constant over time and therefore if these short-term estimates can be extrapolated to a patient’s lifetime. The hybrid design of the ROAR study will immediately generate follow-up periods of up to 15 years per patient. These will still be shorter than the typical 30-year life expectancy of someone diagnosed with a UIA at 50 and there will still therefore be limitations to extrapolation. However, it will be possible to perform repeat searches of the prospectively maintained databases for hospital admissions and deaths at intervals in the future such that ultimately it will yield realistic lifetime estimates.

Long-term follow-up of such a large cohort of patients is only feasible through the use of national databases. A traditional prospective study would be too costly and time consuming to be realistic as well as suffering significant loss to follow-up. The risk posed by using national databases is that patients emigrating are not censored when they leave the country. However, these databases record when patients deregister their general practice at which time they will be censored from further analysis.

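### Censoring at death makes the Cox and Kaplan-Meier absolute risks exceed the probability that rupture actually occurs: slightly at 10 years around age 50, materially at ages 70 to 80

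*Protocol article*

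**What the plan says.** The censoring rule is set for the whole study in the Study design section: "Patients will be censored if there is any occlusive treatment of the UIA or patient death". Objective 1 repeats it, defining the censoring time as "whichever is soonest of the date of treatment, date of death or the HES/PEDW/SMD search date".

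For Objective 2 the model is fixed: "The Cox regression model will be used for risk of rupture". The horizons follow: "The absolute risks can be estimated at relevant time intervals, 2, 5 and 10 years".

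Objective 3 is stated in the Objectives section as "To measure aneurysm rupture risk over time periods >5 years". Its analysis section names the estimators: "This will include Kaplan-Meier and proportional hazards models for univariate and multivariate survival curve fitting". It adds a cumulative hazard plot to see whether the hazard changes with time since diagnosis.

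The Discussion gives the time span: "The hybrid design of the ROAR study will immediately generate follow-up periods of up to 15 years per patient". It hopes that repeat searches mean that "ultimately it will yield realistic lifetime estimates".

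The article does not mention competing risks, cumulative incidence or a model for death. Death records are linked, and under Primary end points a death certified as subarachnoid haemorrhage counts as a rupture. The competing event is therefore death without rupture.

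**The concern.** A patient who dies of another cause can no longer have a rupture. If that death is censored, 1 minus Kaplan-Meier (or 1 minus Cox survival) estimates the risk in a hypothetical population in which nobody dies of anything else. The protocol does not name that as its target. The Patient and public involvement section says that patients care about long-term and ideally lifetime risk, and that treatment decisions are their main concern. For that use, the relevant quantity is the probability that the aneurysm will in fact rupture within the period.

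The gap between the two quantities grows with age and with horizon. Horizon is what Objective 3 is meant to inform, and a personalised model under Objective 2 will be used across ages. Read as the risk a patient faces, death-censored figures would exaggerate what an older patient stands to lose by leaving the aneurysm untreated.

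The censoring rule and the estimators are both written down, so this is a stated choice and not a detail left to an analysis plan.

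**Working it through.** **Inputs from the protocol article**
- Rupture rate from the Sample size section (51 ruptures, 1692 patients, 4.1 years): 51 / (1692 × 4.1) = 51 / 6937.2 = 0.735% per year.
- Alternative rupture rates: 1.4% per year (Introduction) and 60 / 4010 = 1.50% per year (feasibility figures, Sample size).
- Mortality anchor: 30-year life expectancy at age 50 (Discussion). This is the only one given.

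**Reproducing the plan's own figure.** For 60 events: 60/51 × 1692 = 1990.6 patients, and × 4.1 = 8161.4 years. The article states 1990 and 8161, so the rate is the one its authors used. The article gives no figure for the competing-risk point itself.

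**Assumptions.** The rupture hazard λ is constant and the same at every age. Mortality without rupture is Gompertz with slope b, scaled to a mean of 30 remaining years at age 50. The hazards at age 50 are then 0.0063, 0.00399 and 0.00251 per year for b = 0.07, 0.09 and 0.11.

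**Formulas**
- Risk with death censored (what Kaplan-Meier or Cox targets): 1 − exp(−λt).
- Cumulative incidence (what Aalen-Johansen targets): ∫₀ᵗ λ exp(−λu) S(u) du, where S(u) = exp{−(h/b)(exp(bu) − 1)} and h is the death hazard at the starting age.

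**Risks at λ = 0.735% per year, b = 0.09** (death-censored against cumulative incidence)

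| Age | 5 years | 10 years | 15 years |
|---|---|---|---|
| 50 | 3.6% vs 3.6% | 7.1% vs 6.9% | 10.4% vs 10.0% |
| 60 | 3.6% vs 3.5% | 7.1% vs 6.6% | 10.4% vs 9.3% |
| 70 | 3.6% vs 3.4% | 7.1% vs 6.1% | 10.4% vs 8.0% |
| 80 | 3.6% vs 3.1% | 7.1% vs 4.9% | 10.4% vs 5.8% |

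**Ratios over b = 0.07 to 0.11** (from unrounded values)

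| Age | 5 years | 10 years | 15 years |
|---|---|---|---|
| 50 | 1.01–1.02 | 1.02–1.04 | 1.03–1.07 |
| 60 | 1.02–1.04 | 1.06–1.08 | 1.11–1.14 |
| 70 | 1.07 | 1.17 | 1.29–1.33 |
| 80 | 1.15–1.22 | 1.35–1.56 | 1.62–2.04 |

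**Sensitivity to the rupture rate.** At 1.4% per year the ratios hardly move, but the absolute gaps nearly double. At age 70 with b = 0.09, the risks are 13.1% against 11.2% at 10 years (gap 1.9 points, compared with 1.0) and 18.9% against 14.5% at 15 years (gap 4.4 points, compared with 2.4). Results at 1.50% per year are similar.

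**Check without the Gompertz form.** With a constant death hazard μ, cumulative incidence is λ/(λ+μ) × {1 − exp(−(λ+μ)t)}. For μ = 5% per year at 10 years this is 0.00735/0.05735 × {1 − exp(−0.5735)} = 5.6%, against 1 − exp(−0.0735) = 7.1%. A simulation of 200,000 patients gave Kaplan-Meier 7.2% and Aalen-Johansen 5.6% at 10 years, and 10.6% and 7.5% at 15 years. Over μ from 0.5% to 10% per year, the ratio runs from 1.02 to 1.57 at 10 years and from 1.04 to 1.91 at 15 years.

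**The case against.** Five points can be made for the plan.

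1. **Death-censored risk is a legitimate quantity.** It fits a natural-history framing and the comparison with PHASES. Censoring at death is the right cause-specific analysis for hazard ratios and for the cumulative hazard plot. This stands, and those parts should not change. What does not follow is that the same curves give the risk a patient faces, which is the interest the article declares.

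2. **The Objective 3 text does not say that 1 minus Kaplan-Meier will be quoted as an absolute risk, and its list of methods is not exhaustive.** That is fair as to wording. But the objective is to measure rupture risk beyond 5 years, and Kaplan-Meier and proportional hazards are the only estimators named for it. Objective 2 names absolute risks explicitly.

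3. **The gap is small for many patients.** This stands. At age 50 with b = 0.09, the 10-year gap is about 0.2 percentage points. The article gives no age distribution, so the share of patients with a material gap is unknown.

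4. **A reader might infer that the planned analysis will report badly overstated lifetime risks.** The documents do not support that. Present follow-up is at most 15 years, the Discussion concedes limits to extrapolation, and lifetime figures depend on repeat searches for which funding has yet to be sought. The gap would widen in any such later estimate, but that is not a current output.

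5. **A reader might also infer that the reported risks will be too high overall.** That is not shown. About 20% of UK patients are treated, and the Discussion accepts some resulting selection bias. If higher-risk aneurysms are treated, censoring at treatment pulls the estimate down.

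**Conclusion.** The point holds for absolute risk in Objectives 2 and 3, and for the death component only. Whenever some patients die without rupture, the death-censored risk exceeds cumulative incidence. That direction does not depend on the mortality assumed.

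The size does depend on it. It rests on Gompertz mortality tied to one life-expectancy figure and on a constant rupture rate common to all ages. On that basis the excess is negligible to small around age 50 at every horizon to 15 years. It becomes material from about age 70 at 10 years, and is large at age 80, where even the 5-year figure is 15–22% too high in relative terms. Hazard ratios, the cumulative hazard plot and the PHASES comparison are not affected. The change should be made, but it does not undermine the study.

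**What to change.** For absolute risks in Objectives 2 and 3, report cumulative incidence with death without rupture as a competing event, and show it by age:
- Aalen-Johansen curves for the descriptive long-term results.
- Model-based risks from cause-specific Cox models for rupture and for death combined, or from a Fine-Gray model.

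Keep the cause-specific Cox hazard ratios and the cumulative hazard plot as planned. Label any Kaplan-Meier curve as the risk in the absence of death from other causes. Keep the death-censored estimate in Objective 1 so that it matches PHASES.

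The cost is a change of analysis wording and one extra model for death. No new data are needed, since death records are already linked. The drawback is that two risk figures will have to be explained when results are compared with earlier studies. The handling of censoring at treatment is a separate matter that this change does not resolve.
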